### 8.2. POWER CALCULATIONS

Power calculations are based on the means and standard deviation determined for the secondary endpoint from our preliminary data.

### 8.3. STATISTICAL METHODS TO BE UNDERTAKEN

We will use a Generalised linear mixed model with a restricted maximum likelihood function to determine between group differences in the main outcome measures over time, adjusted for randomisation strata. Further analysis will include outcomes as a quantitative measure, using Generalised additive mixed models to examine non-linear (spline) effects of hormone treatments over time, adjusted for randomisation strata. The estimated marginal means across each timepoint plus 95% CI between the groups from baseline to study end will be determined, and p values  $< 0.05$  are considered statistically significant. Following an intention-to-treat protocol, the analysis will include all randomised subjects who are enrolled in the trial.

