#### 2. Secondary endpoints

- Percentage of individuals who have total T levels < 2 nmol/L (above the female reference range) at 3 and 6 months. ;
- Fat mass including leg and gynoid regional fat;
- Patient Health Questionnaire 9 (PHQ-9) (20)
- Gender dysphoria using the Gender Preoccupation and Stability Questionnaire (GPSQ) (21).

**Covariates:** Age and Body Mass Index (BMI, kg/m^2)

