### **6.2. INCLUSION CRITERIA**

1. Male-to-female individuals diagnosed with gender dysphoria according to the DSM-V criteria who are about to commence treatment with anti-androgen therapy, are on E2 and their baseline total testosterone > 10nmol/L (in the male reference range).
2. Aged from 16 – 80 years (individuals with gender dysphoria choosing to access CHT can do so after the age of 16 without requiring parental consent).

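### Section 8.3 models baseline as an outcome visit and does not adjust for the baseline value: this can cost precision on breast volume and leaves the baseline terms of the binary testosterone model without finite estimates

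*Protocol*

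**What the plan says.** Section 8.3 names one model type for the main outcomes, a "Generalised linear mixed model with a restricted maximum likelihood function to determine between group differences in the main outcome measures over time". The only adjustment it lists is for the stratification factors. The synopsis repeats the model. The reported quantities are fixed as follows: "The estimated marginal means across each timepoint plus 95% CI between the groups from baseline to study end will be determined". The baseline value of the outcome is not listed as a covariate, and the text does not say whether the treatment effect is the group-by-time interaction or the between-arm difference at a given visit.

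The next sentence of 8.3 begins "Further analysis will include outcomes as a quantitative measure, using Generalised additive mixed models to examine non-linear (spline) effects". This suggests that the first model also covers outcomes in non-quantitative form. The only outcome defined that way is the testosterone threshold in section 4.3, "Percentage of individuals who have total T levels < 2 nmol/L", which is assessed at 3 and 6 months.

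Section 6.2 requires "their baseline total testosterone > 10nmol/L (in the male reference range"), and section 6.3 excludes those below that limit.

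The primary endpoint in section 4.3 is breast volume, with no time point. The visit table in 5.1 and the procedures table in 5.2 place chest photography and DXA at 0 and 6 months. The heading of 5.4.1, which covers both, gives baseline, 3 and 6 months. Section 8.1 states that no preliminary breast-size data exist.

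**The concern.** Two separate things follow from making baseline an outcome visit.

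For a continuous outcome measured twice, the usual way to express a difference over time is the group-by-time interaction. If the two arms' baseline means are left free, that term is the difference in mean change. Chance baseline imbalance is then subtracted in full rather than in proportion to how well baseline predicts the later value, and precision is lost. The baseline data that would recover it are already being collected. Breast volume is the primary endpoint, and the sample size was not derived from it.

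For the binary testosterone endpoint, baseline carries no information, because nobody can enter the trial below 2 nmol/L. A logistic mixed model with baseline rows has empty event cells in both arms at that visit. The baseline mean with confidence interval that 8.3 promises cannot be produced on the logit scale. Anyone who then reads the arm-by-visit term against baseline would be reading a coefficient with no finite estimate.

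**Working it through.** **The plan's own sample size.** Inputs from section 8.1: 48% v 90%, power 0.9, level 0.05 (two-sided assumed, as the sidedness is not stated), 20% dropout.

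- n per group = [1.960 × √(2 × 0.69 × 0.31) + 1.282 × √(0.48 × 0.52 + 0.90 × 0.10)]² / 0.42² = 23.3, so 24. With 50% v 90% (a 40-point difference) it is 25.4, so 26. The stated 25 lies between.
- 25 / 0.8 = 31.25, so 32 per arm and 64 in total.

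The figures reproduce. They rest on the testosterone threshold and say nothing about breast volume.

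**Breast volume and DXA, visits at 0 and 6 months.** Assume equal variance σ² at both visits, correlation rho, and complete data.

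- Per-person variance of change: 2σ²(1 − rho).
- Per-person residual variance after adjusting for baseline: σ²(1 − rho²).
- Ratio: 2(1 − rho)/(1 − rho²) = 2/(1 + rho).

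The last two columns take 25 completers per arm. The power column shows change-score power where the baseline-adjusted analysis has 80%.

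| Assumed rho | Variance ratio | 50 completers worth | Change-score power |
|---|---|---|---|
| 0.5 | 1.33 | 37.5 | 68% |
| 0.7 | 1.18 | 42.5 | 73% |
| 0.8 | 1.11 | 45.0 | 76% |
| 0.9 | 1.05 | 47.5 | 78% |

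The equivalence was checked on one simulated data set (25 per arm, rho 0.7, two visits):

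| Analysis | Estimate | SE |
|---|---|---|
| REML mixed model, unconstrained group × time | 0.371 | 0.185 |
| Difference in mean change | 0.371 | 0.185 |
| Baseline as covariate | 0.389 | 0.162 |
| Mixed model, common baseline mean | 0.385 | 0.171 |

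The first two rows agree exactly. The last two recover precision.

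**T < 2 nmol/L.** Eligibility (T > 10 nmol/L) gives zero events at baseline in both arms. A random-intercept logistic model was fitted by maximum likelihood to one simulated data set of 25 per arm. The observed proportions were 32% and 52% (spironolactone) against 92% and 96% (cyproterone) at months 3 and 6.

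- Baseline rows kept: the baseline log-odds in both arms ran to the optimiser limit when it was set at −10 and at −20. With the limit at −40 they reached −40 and −23.7 with no change in fit. They have no finite estimate.
- Month-6 log odds ratio with baseline rows: 3.369. Without them: 3.369.

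The failure is therefore confined to the baseline cells and to contrasts built on them.

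**REML.** The criterion is defined for linear mixed models with normal errors. For a binary outcome, software that accepts the request substitutes an approximation such as pseudo-likelihood, so 8.3 does not identify the estimation method for this endpoint.

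**The case against.** The strongest reply is that 8.3 does not name the group-by-time interaction as the test. A mixed model with a common baseline mean fits its wording as well, and such detail is commonly left to the SAP, which is not at hand. That stands in part: the loss of precision depends on which contrast is tested. But 8.3 does fix the adjusters as the randomisation strata and does put baseline among the reported visits, so the protocol as written permits the less precise analysis and omits the baseline value.

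The loss also depends on a correlation that the protocol does not give, and it is small if that correlation is high (ratio 1.03 at rho 0.95). This stands too. If breast volume is also measured at month 3, as the heading of 5.4.1 implies, the exact two-visit result no longer applies automatically.

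A reader might infer that the endpoint on which the trial was sized cannot be tested at all. The documents do not support that. The endpoint is defined at months 3 and 6 only, and 8.3 asks for between-group differences at each time point. In 500 simulated trials (26 per arm, 48% v 90%), the arm-by-month-6 interaction against baseline rejected in 0%, but the month-6 arm contrast rejected in 86%, with or without baseline rows. The 0% belongs to a coefficient the protocol never names.

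A reader might also infer a contradiction between the covariates in 4.3, "Age and Body Mass Index (BMI, kg/m"²), and the strata in 8.3. The strata in section 5.3 are built from those same two variables at randomisation. Any gain from continuous terms would rest on an explained variance that the protocol does not give.

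**Conclusion.** The point holds as one of precision and specification. If breast volume or DXA fat mass is tested by an unconstrained group-by-time term at two visits, the variance is 2/(1 + rho) times what baseline adjustment would give: 33% larger at rho 0.5, 11% at 0.8, 5% at 0.9. This assumes equal variances, complete data and a correlation that is not in the protocol. Under randomisation it is inefficiency, not bias. It deserves attention because the primary endpoint has no power basis and the remedy uses data already collected.

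For T < 2 nmol/L, the baseline mean and any logit-scale change from baseline have no finite estimate, and REML does not define the fit. The month-3 and month-6 arm contrasts are unaffected. No claim is made that pseudo-likelihood would mislead here; that was not tested.

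**What to change.** In section 8.3:

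- **Continuous outcomes.** Add the baseline value of the outcome as a covariate, or constrain a common baseline mean across arms, in the linear mixed model fitted by REML. Keep the strata. Name the month-6 between-arm difference as the primary breast-volume contrast. Continuous age and BMI are optional; if used, specify the baseline values.
- **T < 2 nmol/L.** Fit months 3 and 6 only, by maximum likelihood or logistic regression adjusted for strata. Report the month-6 between-arm difference with its 95% CI. Remove REML and baseline from this model.

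Reconcile the imaging and DXA visits in 5.4.1 with the tables in 5.1 and 5.2, since the number of visits decides the form of the model.

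The cost is wording in 8.3 and the reconciliation of the visit schedule. The analysis changes need no new data and no change in sample size.

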## 9. STORAGE OF BLOOD AND TISSUE SAMPLES

### 9.1. DETAILS OF WHERE SAMPLES WILL BE STORED, AND THE TYPE OF CONSENT FOR FUTURE USE OF SAMPLES

All routine laboratory studies aside from the sex steroid analyses will be performed at Austin Pathology. The results of these tests will go into the participant's Austin Health medical record and be collected separately in their study file. Blood will be discarded within 14 days.

Blood for sex steroid analysis will be collected and couriered to Monash Pathology for analysis via MS/LC-MS. The results of these tests will go into the participant's Austin Health medical record and be collected separately in their study file. The serum estradiol levels will be used for titration of estradiol therapy. Blood samples will be discarded by Monash Pathology within 14 days of analysis.

In collaboration with MCRI, an aliquot of de-identified blood from trial participants will be transferred to MCRI for epigenetic analysis. Blood samples will be discarded within 14 days of analysis.

With additional consent, participants may have their blood stored for future research and genetic testing. The frozen aliquots will be maintained in a locked Austin Health Endocrine Department Laboratory freezer at -80 degrees Celsius indefinitely. These samples will only be labeled with study number and unit record number. Specimen storage will be the responsibility of the PI.

## **10. DATA SECURITY & HANDLING**

### **10.1. DETAILS OF WHERE RECORDS WILL BE KEPT & HOW LONG WILL THEY BE STORED**

Hard copy information will be stored in a locked filing cabinet within a locked office located in the University of Melbourne Department of Medicine, Austin Health.

An electronic database file on REDCap will be kept for each participant and used in real time during study visits to record data. This will also serve as a way to back up hard copy data and analyse collected data. This will be stored on a password/protected file on a University of Melbourne Department of Medicine Server.

Data collection may include asking the participant to fill out a paper-based health information sheet and questionnaires, or alternatively using REDCap. Forms may be sent to the patient in advance of their appointment to complete and discuss at the appointment. The participant would not be provided with any electronic equipment and can only complete this online method if they have access to a personal computer or device.

Electronic and paper study files will be stored for a minimum of 15 years after the end of the study. After that time, electronic information may be permanently deleted and paper records will be destroyed in Austin Health Confidential Waste bins.

### **10.2. CONFIDENTIALITY AND SECURITY**

Hard copy information will be stored in a locked filing cabinet with a locked office located in the University of Melbourne Department of Medicine, Austin Health.

An electronic database file will also be kept for each participant as back up and a way to analyse this information. This will be stored on a password/protected file on a University of Melbourne Department of Medicine Server.

The code to re/identify participants will be kept in a separate password protected file on a Department of Medicine Server. Access to the University of Melbourne Department of Medicine server requires individual log in details and is controlled and monitored.

### 10.3. ANCILLARY DATA

Images from scans will be stored in the participant's Austin Health medical record and in their electronic study file. Chest photography images will only be stored in their electronic study file.

